## Abstract

**Background:**

Formal rehabilitation programs are often assumed to be required after total knee arthroplasty to optimize patient recovery. Inpatient rehabilitation is a costly rehabilitation option after total knee arthroplasty and, in Australia, is utilized most frequently for privately insured patients. With the exception of comparisons with domiciliary services, no randomized trial has compared inpatient rehabilitation to any outpatient based program. The Hospital Inpatient versus HOme (HIHO) study primarily aims to determine whether 10 days of post-acute inpatient rehabilitation followed by a hybrid home program provides superior recovery of functional mobility on the 6-minute walk test (6MWT) compared to a hybrid home program alone following total knee arthroplasty. Secondarily, the trial aims to determine whether inpatient rehabilitation yields superior recovery in patient-reported function.

**Methods/Design:**

This is a two-arm parallel randomized controlled trial (RCT), with a third, non-randomized, observational group. One hundred and forty eligible, consenting participants who have undergone a primary total knee arthroplasty at a high-volume joint replacement center will be randomly allocated when cleared for discharge from acute care to either 10 days of inpatient rehabilitation followed by usual care (a 6-week hybrid home program) or to usual care. Seventy participants in each group (140 in total) will provide 80% power at a significance level of 5% to detect an increase in walking capacity from 400 m to 460 m between the Home and Inpatient groups, respectively, in the 6MWT at 6 months post-surgery, assuming a SD of 120 m and a drop-out rate of <10%.

The outcome assessor will assess participants at 10, 26 and 52 weeks post-operatively, and will remain blind to group allocation for the duration of the study, as will the statistician. Participant preference for rehabilitation mode stated prior to randomization will be accounted for in the analysis together with any baseline differences in potentially confounding characteristics as required.

**Discussion:**

The HIHO Trial will be the first RCT to investigate the efficacy of inpatient rehabilitation compared to any outpatient alternative following total knee arthroplasty.

**Trial registration:**

U.S. National Institutes of Health Clinical Trials Registry (http://clinicaltrials.gov) ref: NCT01583153

## Background

In Australia, inpatient rehabilitation is a costly and commonly utilized treatment option after total knee arthroplasty (TKA), particularly in the private sector. A 12-day inpatient stay in a private facility costs approximately AU$8,100 [1]. Based on unpublished data derived from both the Australian Rehabilitation Outcomes Centre and the National Joint Replacement Registry, approximately 46% of privately insured patients undergoing knee replacement (primary, revision or unicompartmental) in New South Wales, and 32% of private patients Australia-wide, received inpatient rehabilitation in the 2011/12 financial year. As the majority of TKA procedures are performed in the private sector in Australia - some 32,105 per year [2] - the question of whether inpatient rehabilitation yields superior outcomes to cheaper alternatives is of considerable interest to private health insurers and governments alike. Inevitably, the cost of inpatient services is reflected in private insurance premiums and costly premiums negatively affect rates of private health insurance.

### Total knee arthroplasty and associated costs

Between 2003 and 2012, the number of primary TKA procedures undertaken in Australia has increased by 83.7% [2]. This increasing surgical volume is consistent with international trends [3-6]. Demand is increasing due to advances in surgical technique [7], the ageing population and, thus, more people with osteoarthritis (OA), and because consumers are opting for a surgical solution determined to reduce age-related disability in an effort to maintain health and standards of living as they live longer [8,9]. Further increases are expected [2]; thus, there is growing concern regarding the sustainability and affordability of this type of intervention both in the public and private sectors. Increased demand in the public sector cannot be readily met because the supply of services is not driven by demand, but rather is dictated by governmental policy set within the context of a fixed proportion of gross domestic product [8]. Whilst the private sector can adjust more readily to increases in demand, this inevitably puts upward pressure on private health insurance premiums [7]. Whilst the TKA procedure is viewed as highly cost effective in light of the impressive gains in functional performance and health-related quality of life [10,11], the acute care and associated rehabilitative costs impose a significant burden on public and private hospital budgets and resources [12-14]. Not surprisingly, a recent retrospective study from the US concluded that the cost effectiveness of TKA is reduced if the procedure is associated with a stay in an inpatient rehabilitation facility [10].

### Evidence in support of inpatient rehabilitation after total knee arthroplasty

A systematic search of MEDLINE, EMBASE and CENTRAL healthcare databases - first completed in October 2011 and then again in July 2013 (see Table 1 for search strings) - revealed that there was no high level evidence to support the provision of inpatient rehabilitation after TKA over any outpatient-based alternative. Specifically, no randomized trial has compared inpatient rehabilitation to any group-based or center-based one-to-one program or a monitored or unmonitored home program. Two studies (one review [15] and one randomized controlled trial (RCT) [16]) undertaken in the US have concluded that inpatient rehabilitation is not superior to domiciliary rehabilitation (hospital services provided at home). A non-randomized pilot study in Germany concluded that inpatient rehabilitation was not more cost effective compared to outpatient rehabilitation [17]. Longitudinal data from an Australian cohort [13] observed that patient-reported outcomes were similar whether or not TKA patients were discharged to inpatient rehabilitation. The authors concluded that randomized trials were required to explore who, if any group, benefits most (such as older or more infirm patients) from inpatient rehabilitation.

**Table 1 T1:** Medline search string

**No**	**Searches**	**Results**
1	Exp rehabilitation/	147587
2	(rehabilit$ or habilitat$).mp.	115199
3	Exp physical therapy modalities/	121900
4	(Physical therap$ or physiotherap$).mp.	43406
5	1 or 2 or 3 or 4	315967
6	Arthroplasty, replacement, knee.mp.	12403
7	Knee prosthesis/	8491
8	Knee prosthesis/or arthroplasty, replacement, knee/or knee joint/	49918
9	Exp knee/	10214
10	Knee/or knee prosthesis/or athroplasty, replacement, knee/or knee joint/or osteoarthritis, knee/	63871
11	9 or 10	63871
12	Exp arthroplasty/	38632
13	Joint prosthesis/	8761
14	(Arthroplast$ or prosthe$ or replac$).mp.	493605
15	12 or 13 or 14	494353
16	11 and 15	21729
17	6 or 7 or 8 or 16	51109
18	Randomized controlled trial.pt.	380312
19	Controlled clinical trial.pt.	88731
20	Randomi?ed.ab.	332438
21	Placebo.ab.	149978
22	Randomly.ab.	194497
23	Clinical trials as topic.sh.	173251
24	Trial.ti.	120939
25	18 or 19 or 20 or 21 or 22 or 23 or 24	888705
26	Exp animals/not humans.sh.	4007869
27	25 not 26	819207
28	Meta analysis.mp,pt. or review.pt. or search$.tw.	2047494
29	27 or 28	2732075
30	5 and 17 and 29	1316
31	Limit 30 to english language	1212

### Significance

Based on a recent RCT [18] and the lack of research evaluating the necessity of inpatient rehabilitation, we contend that a trial comparing the efficacy of the most resource-intensive form of rehabilitation delivery after TKA - inpatient rehabilitation compared to one with comparatively little resource use such as a monitored home program - is justified. The study will be a landmark study in this area, providing evidence that either supports or refutes the need for resource intensive inpatient rehabilitation after TKA.

### Primary objective

The primary objective of this study is to establish whether inpatient rehabilitation is beneficial after TKA for patients with OA who could otherwise be discharged directly home.

The main hypothesis to be tested by the proposed study is that TKA recipients who receive inpatient rehabilitation in addition to participating in a home program, compared to patients who participate in a home program only, will achieve a superior level of mobility at 6 months post-surgery as assessed by the 6-minute walk test (6MWT).

## Trial design and methods

### Recruitment and consent

We will recruit 140 participants through the Whitlam Joint Replacement Centre (WJRC) at Fairfield Hospital in New South Wales, Australia. Consecutive patients presenting for primary unilateral TKA will be screened for eligibility. Patients not participating in the study will receive usual care (a monitored home program).

To be eligible, participants must meet the following inclusion criteria:

• Undergoing primary, unilateral elective TKA

• Primary diagnosis of OA as documented in the medical record

• Willingness to give written informed consent and willingness to participate in and comply with the study.

• Age 40 years or over

Exclusion criteria will include:

• A history of a mental illness or a condition which would interfere with the patient’s ability to understand the requirements of the study. This may include, but is not limited to, a history of dementia or short-term memory impairment secondary to a cerebrovascular accident.

• A predisposition to be discharged to an inpatient rehabilitation (or hostel) facility due to lack of social support (for example, the patient would otherwise return home with no carer availability) or other physical impairments (for example, contra lateral amputated lower limb).

• Patients unable to read English

• Patients unable to perform a home exercise program without hands-on support from another person or who are unable to perform the program without supervision (that is, observation) from another person.

• Patients restricted to partial or no weight-bearing through the operated limb post-surgery

• Patients experiencing a complication post-surgery which precludes participation in the planned rehabilitation programs (for example, they suffer a stroke or peri prosthetic fracture).

• Pregnancy.

Figure 1 shows the expected flow of participants through recruitment, assessment, intervention and follow-up. The co-ordinating investigator ([name]) will identify potential participants presenting to the WJRC orthopedic clinic, screening consecutive patients against the inclusion and exclusion criteria by chart review and direct questioning. A screening log will be kept, recording the criteria eliminating all those found to be ineligible. A second log will be maintained, detailing reasons for unwillingness to consent to participation in the study by otherwise eligible patients. Those willing to participate will be asked for informed consent using an approved consent form and baseline measures will be obtained.

**Figure 1 F1:**
[figure not shown]
**Cohort ascertainment, randomization and study timeline.** HI, hospital inpatient rehabilitation; HO, hybrid home program.

This trial is a two-arm parallel RCT (Figure 1). The two study groups are: (1) hospital inpatient (HI) and (2) home-based group (hybrid home program (HO)).

Potential participants who are unwilling to undergo randomization will be invited to participate in a third, non-randomized, observational group, who will be followed up 6 months after surgery. This third group will permit the detection of a possible preference effect amongst recruited participants. If study recruitment is biased towards people with a preference for inpatient rehabilitation, there is a risk that participants randomized to the inpatient arm will, in part, report superior outcomes compared to those randomized to the home program because they received their preferred program. If no such superiority is observed when we compare those who were randomly allocated to usual care and preferred inpatient rehabilitation to those who opted to receive usual care (those in the observational arm), then it is possible that any preference effect (if present) is not strong.

The study is expected to take up to 51 months, consisting of 30 to 33 months for recruitment and randomization, 12 months for follow-up of the final participants, and 6 months for analysis.

### Randomization and allocation concealment

Randomization will take place following surgery once it has been confirmed that participants are likely to be cleared for discharge home by post-operative day 5. If it is determined that there is a need for rehabilitation at this time - owing to a post-operative complication - such patients will not be eligible to participate in the study.

A centralized randomization service will be used for participant randomization using a 1:1 ratio, providing secure, coded randomization via telephone. Group allocation, therefore, will be concealed from all parties until the result of the randomization is known. Participants will be randomized to one of the two intervention groups using the method of minimization stratified for variables that affect the primary outcome (distance walked in the 6MWT), age (≤68 years, >68 years), height (≤163 cm, >163 cm), and gender [19].

### Blinding

Outcome assessors will be blind to group allocation, and will not be involved in providing the interventions. The physiotherapists delivering the intervention cannot be blinded to intervention, but will not play a part in the collection or analysis of outcomes, and will only provide one of the treatment options. Those performing the statistical analyses will be blind to group allocation until the evaluation is completed.

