#### Analyses subsets

Data analysis will be completed using the principle of intention-to-treat [36]. We will include all randomized participants regardless of level of compliance with the protocol. The primary outcome variable is distance measured using the outcome of a 6MWT at 26 weeks.

Analysis of covariance will be used for this primary outcome, with treatment group as the main study factor and walking distance at baseline, weight, BMI, co-morbidities and patient preference as covariates. For participants with a missing outcome measure at 26 weeks, an imputation method will be used [37,38].

The secondary outcome variables include the 6MWT at 10 and 52 weeks post-surgery, the 15 m walk test, EQ5D, Oxford Knee Score, KOOS and knee ROM at most post-surgery time points.

Mixed model analyses will be used for the continuous variables measured repeatedly at 10, 26 and 52 weeks to estimate the treatment group by time effects. These analyses incorporate the missing data that may occur at the follow-up occasions. Baseline measurements of the outcome variables, together with factors such as weight, BMI, co-morbidities and patient preference, will be included as covariates [39]. For the binary outcome measured at 10, 26 and 52 weeks (knee flexion ≥100 degrees or ≤100 degrees), a Generalized Estimating Equation model will be used to test the treatment effect, with the adjustment of the covariates as above.

For the analyses involving the observational arm, the change score in the primary outcome will be compared between the observational group and those in the randomized home group adjusting for other covariates. A lack of significant difference in scores between the two groups will suggest there is no strong preference effect in this trial and we may not need to include preference as a covariate in the RCT analyses. To be consistent with the two RCT groups, we will aim for a minimum 64 participants in the observational group.

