For the sensitivity analysis, the above analysis used for the primary and secondary outcome variables will be performed ‘as-treated’, analyzing patients according to the treatment they actually received and excluding those with missing outcome measures. It will only include patients who were compliant with the intervention protocol. Compliance for the HI group will be defined as attendance of a minimum of 7 days of inpatient rehabilitation, along with attendance at no less than two outpatient sessions. Compliance for the HO group will be defined as attendance at no less than two outpatient sessions. There will be procedures put in place to minimize loss to follow-up, such as obtaining multiple contact details at time of consent and reminders that assessments are due. The age, gender and height of participants will be used as stratification variables in the randomization procedure via a minimization algorithm. The mixed model analysis indicated above will include these three variables as additional covariates to incorporate the possible within-treatment group correlation associated with stratification [39].

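### The promised analyst blinding conflicts with a Home-arm comparison on the primary outcome whose result may decide whether preference stays in the RCT models

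*Protocol article*

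**What the plan says.** Two places promise analyst blinding. The Blinding section says "Those performing the statistical analyses will be blind to group allocation until the evaluation is completed". The Abstract (Methods/Design) says of the outcome assessor that this person "will remain blind to group allocation for the duration of the study, as will the statistician". Neither makes an exception for a particular analysis or analyst.

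The Analyses subsets section specifies the primary model as an analysis of covariance of the 26-week 6MWT distance, with treatment group as the study factor and "walking distance at baseline, weight, BMI, co-morbidities and patient preference as covariates". The mixed models and the generalized estimating equation model for the repeated outcomes carry preference as well.

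The same section then says, for the observational arm, that "the change score in the primary outcome will be compared between the observational group and those in the randomized home group", with covariate adjustment. It reads a non-significant result as a sign that there is no strong preference effect, in which case "we may not need to include preference as a covariate in the RCT analyses". The text after Figure 1 gives the reasoning: it sets "those who were randomly allocated to usual care and preferred inpatient rehabilitation to those who opted to receive usual care". It also gives the observational group its follow-up at 6 months, which is the primary end-point.

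**The concern.** Analyst blinding protects the choices still open when the data arrive: which covariates enter, how they are coded and how missing values are imputed. It works only if those choices are closed before anyone making them knows which arm is which.

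Here one such choice, whether preference is in the primary model, is tied to an analysis that uses the primary outcome of one randomized arm, identified by its treatment. If that analysis informs the randomized comparison, the choice is neither blind nor independent of the outcome data. The report could then claim a blind that the plan's own sequence did not keep.

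**Working it through.** The point is one of consistency, so the check sets the statements side by side.

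1. **The blind.** By the Blinding section it lasts until the evaluation is completed. By the Abstract, the statistician's lasts for the whole study. The article does not say which evaluation is meant.

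2. **The comparison.** It uses the observational group and the Home arm only: "compared between the observational group and those in the randomized home group adjusting for other covariates". A/B labels alone do not settle which participants to use. Someone must know which code is Home. With two arms, naming one names the other, so the allocation of all 140 randomized participants (70 + 70) is known to that person.

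3. **The data used.** The variable is change in the primary outcome, and the observational group is followed up at 6 months. The comparison therefore draws on the Home arm's primary end-point data.

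4. **The use of the result.** The primary model lists five covariates: baseline walking distance, weight, BMI, co-morbidities and preference. The comparison may remove the fifth. For its result to bear on that decision, it must be available before the covariate set is final. The article states no timed order, but this one follows from the stated use.

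5. **Taken together.** Steps 2 to 4 place an analysis with the Home arm identified, on primary-outcome data, ahead of the final specification of the primary model. Step 1 says the analysts do not know allocation at that stage. Both cannot be followed as written by the same analysts.

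6. **Can the passages be reconciled without changing the text?** There are three routes:
   - *Run the comparison after the primary model is locked.* The blind holds, but the result can no longer decide the covariate, contrary to the Analyses subsets section.
   - *Give the comparison to a separate, unblinded analyst.* The primary analyst stays blind, but the blinding statements need an exception, and the result still reaches the primary model.
   - *Have a blinded analyst run observational versus A and observational versus B, with a code-holder picking the relevant one.* The labels are hidden at first. If the two results differ in significance, however, the keep-or-drop decision reveals the code. If they agree, the decision still rests on outcome data.

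No stated figure is in dispute. For orientation, the sample size reproduces: n per group = 2 × (1.96 + 0.84)² × 120² / 60² = 62.7, rounded up to 63, and 63 / 0.90 = 70. Nothing in this point changes it.

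**The case against.** The strongest reply is that the blind can be kept in practice. The Sample size section describes an earlier review of results by group made without knowledge of allocation, so the team already works with separated but unlabelled arms. A second analyst or a code-holder could handle the observational comparison. The analysis text lists preference outright and only later mentions possibly leaving it out, which could be read as a simplification considered after the specified model has been run. Who holds the code, and when it is broken, are details that a condensed article may leave to the full protocol or analysis plan.

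Much of this stands. A reader might infer that the analysts cannot stay blind at all. The article does not support that, because workable safeguards exist and the sequence is implied only. What does not fall away is the link itself: each safeguard needs either an exception to the blinding statements or removal of the rule that lets the result shape the covariates. That is a matter of what the published text says, not of a detail left out.

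A reader might also infer that the as-treated analysis breaks the blind, since "Compliance for the HI group will be defined as attendance of a minimum of 7 days of inpatient rehabilitation" while the Home rule counts outpatient sessions only. The article does not support this either. A yes/no compliance flag and a coded treatment-received variable could be prepared by someone outside the analysis, this is a sensitivity analysis that can follow the primary one, and nowhere are the analysts said to receive counts of inpatient days. Diary and cost data are no better evidence: the extent of any cost analysis depends on funding, and nothing places it before the primary test.

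Finally, the primary outcome is a physical test scored by blinded assessors, so measurement is not in question.

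**Conclusion.** The point holds in a limited form. As written, the analyst blinding promised in the Blinding section and the Abstract conflicts with the Home-arm comparison in the Analyses subsets section, because the result of that comparison may settle whether preference remains in the randomized analyses. The consequence is an arm-aware, outcome-dependent choice about one of the five listed covariates in the primary model, and about the same covariate in the repeated-measures models.

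This rests on two assumptions: that the comparison is used as the text says, which puts it before the covariate set is final, and that no separate arrangement for unblinding exists elsewhere. The size cannot be put as a number. The document gives no basis for estimating how much the treatment effect would move with or without preference, and it would be wrong to state a share of the primary analysis as unblinded. The change should be made because it closes an avoidable choice at almost no cost.

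**What to change.** 1. In the Analyses subsets section, keep preference in the primary analysis of covariance as already listed, and delete the option to leave it out on the strength of the observational comparison. That comparison can still be reported as evidence on a preference effect.
2. Release an A/B-coded file first. On it, run and lock the primary analysis of covariance, its imputation, and the mixed and generalized estimating equation models for the randomized groups.
3. Only then break the code for the observational comparison and the as-treated analysis, and state that nothing found there alters the locked analyses.
4. Reword the Blinding section and the Abstract to say that the analysts are blind until that lock.

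The cost is wording, a data release in two stages, and loss of the option to simplify the model. No participants, assessments or analyses are added.
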